##### Neuropathic Pain Symptom Inventory

Neuropathic Pain Symptom Inventory is a self-questionnaire and includes 10 pain descriptors [22]. Intensity is rated on 0 to 10 numerical scales and two temporal items are designed to assess spontaneous ongoing pain duration and the number of pain paroxysms over 24 hours. This questionnaire discriminates five distinct clinically relevant dimensions: spontaneous burning pain, spontaneous deep pain, paroxysmal pain, evoked pain, and paresthesia/dysesthesia.

##### Trail Making Test

This non-verbal cognitive test assesses the ability of speed, executive functions, attention, concentration, and visual perceptual speed [23, 24]. The test takes place in two parts: in Part A, circles are numbered from 1 to 25 and the patient must connect with lines the numbers in ascending order (1-2-3-4, and so forth); in Part B, the circles contain numbers from 1 to 13 and letters from A to L, the patient must connect the circles with lines but alternating numbers and letters (1A-2B -3C, and so forth). The patient must connect the circles as quickly as possible for both parts of the test, without lifting the pen from the paper. The Trail Making Test B additionally provides an estimate of mental flexibility.

##### Digit symbol substitution test

The digit symbol substitution test is a neuropsychological, non-verbal test, which assesses cognitive deficit and brain damage associated with aging and/or depression [25]. It also evaluates learning ability, concentration and attention. It consists of combining pairs of symbols and numbers as quickly as possible and the score is the correct number of symbols in the time allowed (for example, 90 or 120 seconds).

##### Short-Form 36

The Short-Form-36 is a questionnaire evaluating the quality of life of patients [26, 27]. It is a multidimensional scale that assesses the health and quality of life. This scale can be performed in self- or hetero-questionnaire with 36 items including nine dimensions: physical function, role physical, bodily pain, general health, vitality, social functioning, role emotional, mental health and health thinking.

##### Leeds sleep questionnaire

The Leeds sleep evaluation [28, 29] questionnaire is a standardized self-administered questionnaire composed of ten visual analogue scales that relate to four aspects of sleep efficiency: quality of sleep, getting to sleep (visual scales 1, 2 and 3); sleep quality (visual scales 4 and 5); awakening from sleep (visual scales 6, 7 and 8); and behavior following wakefulness (visual scales 9 and 10).

##### Hospital Anxiety and Depression scale (HAD)

The Hospital Anxiety and Depression scale is a self-administered questionnaire in 14 items completed by the patient [30]. It is used to determine the levels of anxiety and depression. Seven of the items relate to anxiety and seven relate to depression.

### Randomization, allocation concealment and blinding

Women with breast cancer are informed by their anesthetist 2 to 3 weeks before mastectomy. On the day of the visit, inclusion and exclusion criteria are verified and written informed consent is obtained by the physician. After clinical examination and pain evaluation, the patient fills in the questionnaires. A clinical nurse independent from the protocol obtains the randomization number from the hospital pharmacy and the patient is then randomized in the memantine or placebo group. Treatment allocation follows a predetermined randomization list and is generated using random blocks. Memantine and placebo treatments are packed in similar blisters covered with an identical label indicating batch number, expiry date and sponsor code with no indication of the name of the drug. The nurse gives the treatment to the patient in an independent room after questionnaires have been filled. In order to maintain blinding, the consent physician (who evaluates pain, the main endpoint of the study) cannot guess allocation at any time and does not see the patient again before they leave hospital.

### Sample size

The number of subjects required is 40 chronic pain patients (20 in each group). The minimum δ difference in numerical scale pain between memantine and placebo groups at 3 months is estimated at 1.6 and σ standard deviation at 1.5, estimated from published data of the literature [31, 32], with α = 0.05 two-sided situation and β = 0.10.

### Statistical analysis

Statistical analyses will be performed with Stata software (version 13, StataCorp, College Station, USA). Concerning the primary objective, comparison between the randomized groups will be performed using an analysis of covariance with baseline score as a covariate [33]. The correlation between baseline and follow-up scores was also proposed. For other secondary parameters, the comparisons between the randomized groups will be performed using the Student test or the Mann–Whitney test (if the conditions for validity of the Student test are not met, normality will be verified by the Shapiro-Wilk and homoscedasticity by the Fisher-Snedecor test). To study the evolution of the main endpoint (numerical scale pain), data analyses will be performed using mixed models which allow us to consider, on the one hand, time, group and interaction time versus group as fixed effects, and, on the other hand, the within- and between-subject variability in order to visualise the assumption of a difference at 2 months between the two randomized groups that increases up to 3 months and stabilizes at 6 months. Residual normality will be checked for all considered models. When appropriate, anticancer chemotherapy (yes/no) will be studied as a fixed effect in these models before considering subgroup analyses. The comparison between the treatment groups will be performed systematically: (1) without adjustment; and (2) by adjusting other factors whose repartition could be, despite the randomization, unbalanced between the treatment groups. The tests will be two-sided, with a type I error set at α = 0.05. A sensitivity analysis of missing data will be performed to ensure the pertinence of the longitudinal data (MAR (Missing at random) or MCAR (Missing completely at random)). In order to assess the problem caused by missing longitudinal data at 6 months, estimation methods developed by Verbeke and colleagues [34] will be proposed.

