## Methods/Design

We are conducting a randomized, placebo-controlled clinical trial in the Oncology Hospital, Clermont-Ferrand, France, in 40 women undergoing total mastectomy for breast cancer. The study has been approved in December 2011 by the regional Ethics committee (CPP Sud-Est, France, number AU917) and registered on 16 February 2012 at “http://www.clinicaltrials.gov” (NCT01536314). Women provide written informed consent prior to their participation in the study during their anesthesiology visit. After baseline assessments (day (D)_−15_) of pain intensity, cognition, quality of life and quality of sleep questionnaires, participants are randomized into two parallel groups: memantine (n = 20) or placebo (n = 20). Memantine or placebo (lactose) is given orally for 4 weeks starting 2 weeks before surgery. Memantine is given in increasing doses: 5 mg/day for 3 days; 10 mg/day for 3 days; 15 mg/day for 3 days and 20 mg/day for 5 days. Endpoints are reassessed 15 days (D_0+15_), 3 months (D_0_ + 3 months) and 6 months (D_0_ + 6 months) post-mastectomy. In order to maintain a good compliance and to verify that women do not develop adverse events, patients are called once a week by phone. A booklet for monitoring is completed daily by the patient for 6 months from the day of surgery. Detailed information on the present study is summarized in Figure 1.

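### For secondary outcomes measured before randomisation, the plan neither says which score is tested nor prespecifies the outcome's own baseline as a covariate, unlike for the primary endpoint

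*Protocol article*

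**What the plan says.** In the protocol article, Statistical analysis, the primary comparison is fixed as follows: "comparison between the randomized groups will be performed using an analysis of covariance with baseline score as a covariate". The rule for the remaining outcomes is different: "For other secondary parameters, the comparisons between the randomized groups will be performed using the Student test or the Mann–Whitney test". The choice between the two tests depends on checks of normality and equal variance. The variable entering the test is not named. Mixed models are planned for numerical-scale pain only.

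The same section adds a general step: group comparisons are made first unadjusted, then adjusted for factors that turn out to be unevenly distributed between the arms.

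Baselines exist for most of these outcomes. Methods/Design places the baseline assessments "of pain intensity, cognition, quality of life and quality of sleep questionnaires, participants are randomized into two parallel groups". Table 1 marks Trail Making, Digit Symbol, SF-36, Leeds, HAD and DN4 as done at the D0-15 visit, and the randomisation section has the questionnaires completed before treatment is allocated. NPSI, BPI and McGill have no D0-15 value.

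**The concern.** Maintaining cognition and quality of life is a stated aim in the Abstract and Background, yet the trial is sized for pain alone. With 20 women per arm, the cognitive, quality-of-life, sleep and mood comparisons need whatever precision the data can give. A baseline taken on the same instrument is an obvious source of it, and the plan already uses that device for the primary endpoint.

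Two things are left unsettled for the secondary outcomes. First, follow-up scores and change scores both fit the text, and they can give different answers and different power. Second, the outcome's own baseline enters a model only if it happens to look unbalanced. The precision gain from a baseline comes from its correlation with the outcome, whether or not the arms differ at the start, so an imbalance trigger does not secure it.

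**Working it through.** **The plan's own figure.** Inputs from Sample size: "The minimum δ difference in numerical scale pain between memantine and placebo groups at 3 months is estimated at 1.6"; "σ standard deviation at 1.5, estimated from published data of the literature"; "with α = 0.05 two-sided situation and β = 0.10". Normal approximation: n per arm = 2 × (1.960 + 1.282)² × (1.5/1.6)² = 18.5, so 19. The noncentral t calculation gives 20 per arm, with power 0.908. The stated 20 per arm reproduces. It concerns the primary endpoint only; no effect size, SD or power is stated for any secondary outcome.

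**Inputs for the secondary outcomes.**
- n = 20 per arm (Sample size).
- Two-sided 0.05 (Statistical analysis): "The tests will be two-sided, with a type I error set at α = 0.05".
- Effect d = 0.7 SD: assumed.
- Correlation r between baseline and follow-up: assumed, 0.3 to 0.8. The article mentions looking at this correlation but gives no value.
- Equal SD at baseline and follow-up: assumed.

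**Formulas.** Power comes from the noncentral t distribution with noncentrality d′ × √(20/2), where d′ is:
- follow-up score, t-test: d′ = d, 38 df;
- change score, t-test: d′ = d / √(2(1 − r)), 38 df;
- ANCOVA: d′ = d / √(1 − r²), 37 df.

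Example at r = 0.5: the ANCOVA d′ is 0.7/√0.75 = 0.808 and the noncentrality is 0.808 × √10 = 2.56, giving power 70%. For follow-up scores the noncentrality is 0.7 × √10 = 2.21, giving 58%.

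| r | 1 − r² | Follow-up t-test | Change-score t-test | ANCOVA | Gain over follow-up (points) |
|---|---|---|---|---|---|
| 0.3 | 0.91 | 58% | 45% | 62% | 4 |
| 0.5 | 0.75 | 58% | 58% | 70% | 12 |
| 0.6 | 0.64 | 58% | 67% | 77% | 19 |
| 0.7 | 0.51 | 58% | 80% | 86% | 28 |
| 0.8 | 0.36 | 58% | 93% | 95% | 37 |

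The ANCOVA formula ignores the small cost of chance differences in baseline means. Simulated trials with these inputs gave 70% at r = 0.5 and 84% at r = 0.7, so the column may be a point or two generous.

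**Other effect sizes.** At d = 0.5 the follow-up t-test has 34% power; ANCOVA has 37%, 43%, 49%, 58% and 73% at the same five values of r. At d = 0.8 the figures are 69% against 73%, 81%, 87%, 93% and 98%. The pattern is the same.

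**Which score is tested matters.** Change scores do worse than follow-up scores below r = 0.5, equal them at 0.5, and come close to ANCOVA at high r. ANCOVA has the highest power of the three at every r in the table, so it is the choice that does not depend on guessing r.

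**The case against.** A reader might infer that the plan throws the baselines away and so loses a large part of its power. The article does not support that.

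- It never says follow-up scores are what is tested. If change scores are meant, the baseline is used, and at r = 0.8 the shortfall against ANCOVA is only 2 points (93% against 95%).
- The adjusted second step could bring in a baseline that looks unbalanced, so chance differences are not simply left in every estimate.
- No correlation is given. Surgery, and chemotherapy in some women, come between baseline and follow-up, so a low r cannot be excluded. At r = 0.3 the gain over follow-up scores is 4 points.

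These points limit the size of the concern but do not remove it. The tested variable remains unnamed, and adjustment triggered by observed imbalance is no substitute for a prespecified prognostic covariate.

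A reader might also object to choosing the test by normality and variance checks. No harm from that is shown here: in simulation the two-stage procedure had 58% power at 0.7 SD, the same as the plain t-test, and a type I error of about 5%. The rule is stated in advance, and this point does not ask for it to be removed.

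Finally, these outcomes are secondary, unadjusted tests in a randomised trial are valid, and a condensed article may leave detail to a fuller document. That is fair for modelling detail such as transformations. But the article does state a test for these outcomes, and that test cannot include a covariate.

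**Conclusion.** The point holds as one of efficiency and prespecification, not validity. The primary analysis is unaffected. For Trail Making, Digit Symbol, SF-36, Leeds and HAD, the plan should name the score tested and fix the outcome's own baseline as a covariate.

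The size depends on r. At 0.7 SD and 20 per arm, the gain over follow-up scores runs from 4 points (r = 0.3) to 37 points (r = 0.8), and is large only from about r = 0.6. If change scores are intended, the gain runs the other way, from 17 points at r = 0.3 to 2 points at r = 0.8. Both r and the effect size are assumptions. The change is worth making because it uses data already collected.

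**What to change.** In Statistical analysis, state that for each continuous secondary outcome with a D0-15 value the main comparison is an ANCOVA of the follow-up score on treatment group and that outcome's baseline, reported as an adjusted difference with its 95% confidence interval. Keep the Student or Mann-Whitney test for outcomes without a baseline (NPSI, BPI, McGill) and as a supporting analysis elsewhere, and name the score to which it applies. DN4 has a baseline but is a 0 to 10 count read against a cut-off of 4, so it need not be forced into the linear model.

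The cost is a sentence or two of text, with no new data, visits or patients.

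### Secondary scores: the test is chosen by pre-tests on the trial's own data, and unequal variances are sent to Mann-Whitney, which does not remedy them, so error for a difference in means can exceed 5% when spreads differ

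*Protocol article*

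**What the plan says.** The rule is in the Statistical analysis section of the protocol article. For secondary parameters, "the comparisons between the randomized groups will be performed using the Student test or the Mann–Whitney test". A bracket makes the choice depend on whether Student's assumptions hold and says how that is judged: "normality will be verified by the Shapiro-Wilk and homoscedasticity by the Fisher-Snedecor test". The bracket is loosely worded, but the natural reading is Student by default and Mann-Whitney if either check fails. No third test, such as an unequal-variance t test, is offered. No significance level is given for the checks, and nothing is said about keeping the same test for a score across visits.

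The same section sets the level: "The tests will be two-sided, with a type I error set at α = 0.05". The Methods/Design section gives the arms as "memantine (n = 20) or placebo (n = 20"). The Objectives section asks for secondary results at both 3 and 6 months.

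The rule does not govern the primary endpoint, which is analysed by ANCOVA, or the course of pain intensity over time, which is analysed by mixed models. It covers cognition, quality of life, sleep, anxiety and depression, and the NPSI, BPI and McGill scores.

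**The concern.** There are three faults.

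- **The variance branch leads to the wrong test.** Mann-Whitney's null hypothesis is that the two distributions are identical. When spreads differ it does not keep its level as a test of a difference in means. With equal arms, Student's test is already close to its nominal level under unequal variances, so the rule replaces a nearly valid test with a less valid one.
- **The choice depends on the data.** Which hypothesis is tested, means or distributions, is settled by the same 40 values that are then tested.
- **The choice can differ between visits.** If the checks are run visit by visit, one questionnaire may be compared by means at 3 months and by ranks at 6 months. The two p-values would then answer different questions.

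At stake is how the secondary results are read. A significant result may be taken as a difference in mean score when the arms differ only in spread or shape. For NPSI, BPI and McGill, Table 1 shows no screening value, so a baseline-adjusted comparison is not available as a substitute.

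**Working it through.** **The plan's own figure.** The article states "σ standard deviation at 1.5", a difference of 1.6 points, and "with α = 0.05 two-sided situation and β = 0.10". The normal formula gives n per arm = 2(1.960 + 1.282)² × (1.5/1.6)² = 18.5, so 19. The t-based calculation gives 19.5, so 20, with power 90.8% at 20 per arm. The stated 20 per arm is reproduced and is the size used below. The article gives no operating characteristics for the secondary rule.

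**Assumptions, because the article gives none.** Each pre-test is at 5%. Shapiro-Wilk is run in each arm, and the variance test is a two-sided F test. SD ratios and score shapes are assumed. There were 20,000 simulated trials per scenario, so the Monte Carlo standard error near 5% is √(0.05 × 0.95/20,000) = 0.15 points.

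**How often the rule switches to Mann-Whitney (normal scores, 20 per arm).**
- Equal SDs: 1 − 0.95³ = 14.3% if the three checks were independent; simulated 14.6%.
- SD ratio 2: the F test (critical value 2.53 on 19 and 19 df) rejects in 83.7% of trials. With the two Shapiro-Wilk checks, 1 − (1 − 0.837) × 0.95² = 85.3%; simulated 85.6%.
- SD ratio 3: simulated 99.7%.

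**Rejection rate at nominal 5%, with equal true means.**

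| Scenario | n | Planned rule | Student | Welch |
|---|---|---|---|---|
| Normal, equal SD | 20/20 | 5.3% | 5.2% | 5.2% |
| Normal, SD ratio 1.5 | 20/20 | 5.6% | 5.3% | 5.1% |
| Normal, SD ratio 2 | 20/20 | 5.9% | 5.2% | 5.0% |
| Normal, SD ratio 3 | 20/20 | 6.9% | 5.5% | 5.0% |
| Normal, ratio 2, larger SD in smaller arm | 20/16 | 7.0% | 6.9% | 5.1% |
| Normal, ratio 3, larger SD in smaller arm | 20/16 | 8.2% | 8.2% | 5.3% |
| Normal, ratio 2, larger SD in larger arm | 16/20 | 5.1% | 3.8% | 5.1% |
| Gamma, equal means, SD 0.5 and 1 | 20/20 | 17.1% | 6.4% | 6.3% |
| Lognormal, same in both arms | 20/20 | 4.6% | 4.2% | 3.9% |
| Exponential, same in both arms | 20/20 | 4.9% | 4.8% | 4.6% |
| Floor-heavy 0–10 scale, same in both arms | 20/20 | 5.1% | 5.0% | 4.9% |

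A second set of runs gave 5.8% and 6.9% for the rule at SD ratios 2 and 3, against 5.0% and 5.5% for Welch. At ratio 3 with 20 per arm the rule also has about 2 to 3 points less power than Welch (75.2% against 78.4% in one run).

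**Why the gamma row is so large.** Take X exponential with mean 1 and Y gamma with shape 4 and mean 1. Then P(X < Y) = 1 − (1 + 1/4)⁻⁴ = 1 − 0.41 = 0.59, although the means are equal. Mann-Whitney is responding to this departure from 0.50. That is a real difference in distribution but not a difference in means.

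**Different tests at the two visits.** Assume the checks are run separately at each visit. With normal scores and equal SDs, independence between visits would give 2 × 0.143 × 0.857 = 24.5%. Simulation with a within-patient correlation of 0.5 or 0.7 gives 23 to 24%. Over normal and lognormal scores with SD ratios 1 and 1.5, the range is about 20% to 44%.

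**The case against.** A reader might infer that the secondary tests generally run above 5%. The article does not support that. If memantine has no effect at all, randomisation gives both arms one distribution, and the rule then rejects in 4.6% to 5.3% of trials. The excess needs arms that differ in spread while their means are equal. The largest figure, about 17%, needs an assumed skewed shape with exactly equal means, and Welch is not at 5% there either (6.3%). With normal scores and 20 per arm the excess over Welch is 1 to 2 points. This stands, and it limits the claim.

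A reader might also infer that Welch should replace the rule for every score. That does not follow. A drug that takes many women to the floor of a scale lowers the mean, so the issue there is power, and ranks do better. Under assumed floor-heavy scores the planned rule had 70.8% power against 61.9% for Welch, and under a lognormal shift 67.3% against 49.7%. This stands too, and it shapes the fix.

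A third inference is that the plan prescribes different tests at 3 and 6 months. It does not. The article neither says that the checks are run per visit nor gives their level. It leaves the possibility open, and a change of test would not stop means and confidence intervals being reported at each visit.

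Finally, the section promises each comparison with and without adjustment, so the two-sample test is not the only analysis, even for NPSI, BPI and McGill. None of this answers the central fault: the fallback does not address the failed assumption that triggers it.

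**Conclusion.** The point holds in a limited form. The rule chooses the test from the data and sends unequal variances to a test that does not correct for them. For a difference in means, the error rate can rise to about 6 to 7% for normal scores at SD ratios of 2 to 3 with 20 per arm, against about 5 to 5.5% for Welch. It can go higher for skewed scores with equal means, or if dropout leaves the more variable arm smaller. It stays near 5% when the arms share one distribution. The rule also permits a change of test between visits, although it does not state one. All sizes rest on assumed distributions, pre-test levels and correlations. Only secondary scores are concerned, so this is worth correcting but does not threaten the trial's main conclusion.

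**What to change.** Delete the Shapiro-Wilk and Fisher-Snedecor gate and fix one test per score, used at every visit, before unblinding.

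- **Roughly symmetric scores** (for example SF-36, HAD, Digit Symbol Substitution Test, Leeds): Welch's t test, with the mean difference and its 95% CI.
- **Scores expected to be floor-heavy or strongly skewed** (for example NPSI, McGill): a rank test named in advance, read as a comparison of distributions and not of means.
- **Remaining continuous scores**: assign each to one of these two groups in the same list.

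The cost is a sentence or a short table in the analysis plan, and no new data. When variances are equal, Welch holds its level as Student does (5.2% each in the table). The downside is small: if a score's shape is misjudged, the fixed choice may lose some power.

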**Methods/Design:**

A randomized clinical trial (NCT01536314) includes 40 women with breast cancer undergoing mastectomy at the Oncology Hospital, Clermont-Ferrand, France. Memantine (5 to 20 mg/day; n = 20) or placebo (n = 20) is administered for 4 weeks starting 2 weeks before surgery. Intensity of pain, cognitive function, quality of life and of sleep, anxiety and depression are evaluated with questionnaires. The primary endpoint is pain intensity on a 0 to 10) numerical scale at 3 months post-mastectomy. Data analysis is performed using mixed models and the tests are two-sided, with a type I error set at α = 0.05.

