#### Secondary endpoints

Secondary endpoints are the evaluation of pain at the screening visit, at 2 weeks, 3 months and 6 months after mastectomy (numerical scale, Brief pain Inventory, McGill pain questionnaire), neuropathic pain (Neuropathic Pain in 4 questions, Neuropathic Pain Symptom Inventory), cognition (Trail Making Test, Digit Symbol Substitution Test), sleep (Leeds sleep questionnaire), quality of life (Short-Form-36), and anxiety and depression (Hospital Anxiety and Depression scale). The summary of the different evaluations for a patient is reported in Table 1.

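### The longitudinal mixed model for numerical-scale pain has no baseline term, although the primary ANCOVA on the same scale does; adding the screening score costs almost nothing and can only help coherence, with a precision gain that depends on an unstated correlation

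*Protocol article*

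**What the plan says.** Under Statistical analysis, the primary 3-month result is fixed as follows: "comparison between the randomized groups will be performed using an analysis of covariance with baseline score as a covariate". Later in the same paragraph the plan turns to the course of the same scale: "To study the evolution of the main endpoint (numerical scale pain), data analyses will be performed using mixed models". The fixed effects given for these models are "time, group and interaction time versus group as fixed effects". The stated aim is to display a between-group difference that grows up to 3 months and then holds at 6 months.

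Two other sentences in that paragraph touch on covariates. One says that "anticancer chemotherapy (yes/no) will be studied as a fixed effect in these models". The other says comparisons are made first unadjusted and then "by adjusting other factors whose repartition could be, despite the randomization, unbalanced between the treatment groups". Neither names screening pain.

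The Secondary endpoints section reads: "Secondary endpoints are the evaluation of pain at the screening visit, at 2 weeks, 3 months and 6 months after mastectomy (numerical scale". Table 1 confirms that the numerical scale is recorded at screening. The section on randomization, allocation concealment and blinding places the pain evaluation before the randomisation number is obtained. The article does not say whether the screening score enters the mixed model as a response visit, or which contrast will be read from it.

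**The concern.** One paragraph treats the baseline of one outcome in two ways. The ANCOVA conditions on it; the mixed model, as listed, does not.

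There are two ways to read the model, and neither uses the screening score efficiently.

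- If screening is a response visit, a free group term lets the arms have different baseline means, although randomisation makes the expected difference zero. The time-by-group contrast is then a difference in change from screening. The group difference at a single visit takes nothing from baseline when data are complete.
- If screening is left out of the response, the model ignores it altogether.

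What is at stake is the precision of the 3- and 6-month differences in a secondary analysis, and agreement between two analyses of the same 3-month data. With 40 women there is little precision to spare. No bias is involved.

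**Working it through.** **Inputs from Sample size.** Difference 1.6, SD 1.5, two-sided alpha 0.05, beta 0.10, 20 per arm.

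**Assumed, because the article gives no figure.** Rho, the correlation between screening and follow-up pain, is varied. The screening SD is taken first as 1.5 and then as half of that. The difference of 1.6 is also taken to hold at 6 months, in line with the article's expectation that it stabilises.

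**Step 1: reproduce the plan's sample size.** The normal approximation gives n per arm = 2(1.960 + 1.282)² × (1.5/1.6)² = 18.5, so 19 per arm (38 in total). The exact noncentral t gives 89.2% power at 19 per arm and 90.8% at 20. The stated 20 per arm is therefore right.

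**Step 2: standard errors of the group difference, n = 20 per arm.**

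- Group difference at a visit, no baseline: 1.5 × √(2/20) = 0.474 at every rho.
- Change from screening, equal SDs: 1.5 × √(2(1 − rho) × 2/20).
- Baseline-adjusted: 1.5 × √((1 − rho²) × 2/20), multiplied by √(1 + 1/36) for estimating the slope in 40 patients.

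| rho | Visit difference, no baseline | Change from screening | Adjusted | Adjusted, small-sample factor |
|---|---|---|---|---|
| 0.2 | 0.474 | 0.600 | 0.465 | 0.471 |
| 0.3 | 0.474 | 0.561 | 0.452 | 0.459 |
| 0.5 | 0.474 | 0.474 | 0.411 | 0.416 |

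Generalised least squares on a four-visit model (compound symmetry, complete data) gave the same values. With a free group term at screening, the 3-month visit difference has SE 0.474 and the time-by-group contrast has the change-from-screening SE. With a common mean at screening, the SE equals the adjusted column (without the small-sample factor).

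**Step 3: power for a difference of 1.6.** Noncentral t, with 38 df unadjusted, and 37 df plus the small-sample factor adjusted.

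| rho | Visit difference, no baseline | Change from screening (screening SD 1.5) | Adjusted |
|---|---|---|---|
| 0.2 | 90.8% | 74% | 91.1% |
| 0.3 | 90.8% | 79% | about 92.5% |
| 0.5 | 90.8% | 91% | 96.2% |

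**Step 4: break-even for the visit difference.** Adjustment gains once (1 − rho²)(1 + 1/36) < 1. That is rho > √(1 − 36/37) = 0.164. Below about 0.16 there is no gain.

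**Step 5: sensitivity to the screening SD.** If the screening SD is k times the follow-up SD, the change contrast has variance factor 1 + k² − 2k·rho. With k = 0.5 and rho = 0.2 this is 1 + 0.25 − 0.20 = 1.05, against 1 − 0.04 = 0.96 adjusted. The ratio is 1.09. With k = 1 it is 1.60/0.96 = 1.67. Power at k = 0.5 and rho 0.2 is about 89%, against 91% adjusted. At rho 0.3 the variance ratio is 0.95/0.91 = 1.04.

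**The case against.** The strongest reply has four parts.

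- **The contrast.** The large loss needs two things the article does not state: that screening is a response visit, and that change from screening is the contrast read. The stated aim describes group differences at post-surgery times. This stands. A reader might infer from 74% against 92% at rho 0.2 (the adjusted figure before the small-sample factor) that the trial gives up nearly 20 points of power. The documents do not support that. The figure belongs to one contrast under one assumption about the screening SD. Eligibility does not require pain at entry, so the screening SD could well be lower.
- **Low correlation.** Pain before surgery may correlate only weakly with pain 3 months later, and then the visit-specific difference loses almost nothing. This also stands. Low rho is the worst case only for the change contrast.
- **The list may be open.** The effects are worded as ones the models allow to be considered; chemotherapy may be added, and an adjusted comparison is promised. This stands only in part. Chemotherapy is a different variable, and the adjustment is triggered by imbalance and does not name screening pain. A prognostic baseline is worth using whether or not it is imbalanced.
- **Detail for an unseen plan.** An article may leave covariance structure and visit lists to the full protocol. But it does state the fixed effects here, and for the primary analysis of the same scale it states the baseline covariate. The point concerns that stated specification and does not rest on anything being absent.

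A reader might also infer that this model is the only analysis of pain from baseline to 6 months. The article does not say so: 6-month pain could also fall under the Student or Mann–Whitney comparisons of other secondary parameters. The abstract's general sentence, "Data analysis is performed using mixed models", does not displace the ANCOVA as the primary analysis.

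**Conclusion.** The point holds as a matter of precision and coherence in a secondary analysis. The stated mixed model has neither a baseline covariate nor a common-baseline constraint, while the primary analysis is an "analysis of covariance with baseline score as a covariate". Its 3- and 6-month group differences are generally no more precise than adjusted ones, and its 3-month estimate can depart from the ANCOVA without need.

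If differences are read at each visit, which is what the wording suggests, the gain from adjusting is 0.3 points of power at rho 0.2, under 2 at rho 0.3 and 5.4 at rho 0.5. Below rho of about 0.16 there is none. If change from screening is read and the screening SD is 1.5, the gain is about 17, 13 and 5 points at the same values, and far less if the screening SD is lower. Rho and the screening SD are assumptions throughout, and the calculations assume complete data. The primary comparison, the type I error and the sample size are not affected.

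**What to change.** Reword the mixed-model sentence in one of two equivalent ways.

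- Take the post-surgery scores (D0+15, 3 months and 6 months) as the response, with group, categorical time, group-by-time, the screening numerical-scale score and its interaction with time as fixed effects.
- Keep screening as a response visit, but give both arms a common mean there.

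In either case, report the group difference at each visit. With complete data this brings the 3-month result into line with the primary ANCOVA.

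The cost is one sentence and one to three degrees of freedom for the baseline terms. It needs no new data and no extra patients.
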